#### Information-seeking behaviour questionnaire (Q4) (at three months, and four years)

Based on previous research conducted by our research team on French cancer survivors’ living conditions, we decided to explore women's information-seeking behaviours. This research showed that patients’ comprehension of information provided is related to their information-seeking behaviours [28]. Patients who did not understand information provided by healthcare professionals, as well as patients who did not obtain responses to their questions, were obliged to search for information on their own, especially in the case of patients with a low socioeconomic status who might perceive themselves as “dropouts” of the healthcare system. To investigate these information-seeking behaviours, we adapted the questionnaire that was developed in this previous research and added five questions from the Health Literacy Questionnaire (HLQ) focused on the “search for information” dimension [43], keeping in mind the previously described trend for an association between inadequate health literacy and lower breast cancer screening rates [44].

Our questionnaire asks whether women searched for information in the first place, their reasons for doing so, and the type of information they looked for (e.g., on the internet, in the media, or by asking healthcare professionals). Some questions also relate to breast cancer screening in general, and to risk-stratified breast cancer screening issues in particular.

As this questionnaire was developed for use in this specific study, the questions were piloted (with the exception of the five questions of the HLQ questionnaire already validated) amongst the same group of ten women and with the same methods as the ones used for the comprehension questionnaire.

The information-seeking behaviour questionnaire is administered at three months and four years to all participants of MyPeBS.

#### Risk perception and behaviour change (Q5) (at baseline, three months, and four years)

As previously underlined, it is essential that all decisions made as part of breast cancer screening are informed and based on sound understanding of good quality information provided. A key element of understanding is how accurately women perceive their own risk of breast cancer following risk-stratified screening, and whether this has been improved, relative to standard screening. For these reasons, we will assess perception of risk of breast cancer, and perceptions of efficacy and risks of different prevention options, to assess the constructs of Protection Motivation Theory, a theory that aims to understand how risk information can translate into behaviour change or not [45]. Uptake of options that may reduce future risk of breast cancer such as increased frequency of mammography in women at high risk, or increases in healthy eating or physical activity, is linked to perceptions of the risk of disease and benefits of these behaviours in reducing risk [11]. By contrast, a potential harm of risk-stratified screening is that those who are told they are low risk may increase their unhealthy behaviours through being falsely reassured (i.e., a certificate of health effect).

To estimate comparative risk and comparative severity scores, participants are asked to choose a category indicating their perceived risk of invasive breast cancer over the next ten years, compared to the population’s average (comparative risk). They are also asked to evaluate, if they were to get breast cancer, how severe they think this would be (comparative severity) on a five-point scale from lower to higher risk.

The behaviour change questions evaluate three different behaviours relating to reducing breast cancer risk: improving diet, increasing physical activity and attending mammography appointments. Five-point scales are used to measure Response Efficacy (the perception of how much the behaviour would reduce the participant’s risk of breast cancer) and Self-Efficacy (how easy or difficult it would be to enact these behaviours). To calculate the intention to change behaviour scores, participants are asked three questions assessing their intention to change the three health-related behaviours on a five-point scale, from “strongly disagree” to “strongly agree” [22].

#### Quality of life (Q6) (at baseline and four years)

To assess women’s quality of life, we use the EQ-5D licensed by EuroQoL research foundation. This European quality of life tool is a validated pre-scored multi-attribute health status scale that has been used in a wide range of populations and situations, including breast cancer screening [46–49]. It is short and easy to complete. It is divided into two parts: a first part with five items representing five dimensions, i.e. mobility, self-care, usual activities, pain and discomfort, anxiety and depression. The patient is asked to respond on a five-point scale: 1, no problem; 2, mild problems; 3, moderate problems; 4, severe problems; 5, extreme problems or total disability. A second part with a visual analog scale “EQ-5D VAS”, a 20-cm line graduated from 0 to 100 allows the patient to rate his or her current health status, with 0 being the worst health status and 100 the best.

The EQ-5D is administered at baseline and at four years to analyse and compare women’s quality of life between the two screening options, i.e. standard versus personalised breast cancer screening, and between groups of different risk levels. We will thus explore whether women who underwent risk-stratified screening have a better quality of life than women who underwent standard screening. Quality of life among different socio-economic subgroups will also be compared and related to breast cancer screening compliance, using both aggregated and unaggregated measures (i.e. considering the five dimensions of the EQ-5D separately) of quality of life, based on the responses to the EQ-5D questionnaire.

#### Trial Programme Satisfaction (Q7) (at one year and four years)

This questionnaire is an evaluation of the overall satisfaction of women with their participation in the study, with the information provided and communication tools used, and with the overall organisation of the trial. The intention to participate in the study is assessed at one year and actualised at four years. Analyses will consider the dropout rate. The questionnaire is an adapted version of a satisfaction questionnaire on organisation of the screening process and the information received, validated by Bairati et al. [29] and currently used in Canada. The questionnaire was modified to integrate specific questions concerning the MyPeBS study. It was validated along with the comprehension and information-seeking behaviour questionnaires, following the same methodology, and consists of seven questions with five-point scale answers.

#### Socio-demographic questionnaire (Q8) (at baseline and four years)

The characteristics of women participating in MyPeBS versus those taking part in the current population-based screening programmes will be analysed and compared, in terms of socio-demographics (age, education level, profession, income level, geographic area, marital status) and socio-economic status. In particular, we will focus on social inequalities by using the nine items version of the Material Deprivation Index (MDI), keeping in mind that socio-economic deprivation is a well-established determinant for low uptake and low compliance to cancer screenings [50] including breast cancer screening [51].

The MDI is an aggregated measure of deprivation validated in many European countries, based on the EU-SILC survey that has already been used to assess inequalities in cancer screening access [52]. This index has been the most used in the literature to assess material deprivation and make international comparisons. This index has several strengths: (i) the multi-dimensionality of the nine-items MDI has been psychometrically validated, (ii) it is theoretically justified, in particular because it makes the distinction between lack of items (due to choice) and enforced lack of items because of poor economic resources, (iii) validated threshold values are derived to classify individuals into “material deprivation” or “severe material deprivation”, (iv) the proportion of materially deprived individuals in twenty-seven European countries has been calculated based on the EU-SILC survey, thus allowing for comparison of representativeness of MyPeBS participants.

The MDI score is calculated by scoring 1 if the person answers “no, I cannot afford it” to the item and then by summing all items (thus the MDI ranges between 0 and 9). A threshold value of three of the MDI is used to classify individuals into “material deprivation” and a threshold of is used to classify individuals into “severe material deprivation”.

The impact of socio-demographics and deprivation levels on women's adherence to schedule during the trial will be analysed. Women’s socio-demographic and socio-economic characteristics will be analysed at baseline and four years and will be compared to the characteristics of women taking part in the current population-based screening.

### Qualitative interview guide

Participants will be asked about how acceptable they found the risk-stratified process, their understanding of the purpose of each phase, how they experienced receiving their risk category, if they would recommend this type of screening to their friends or family, and how the process could be improved. Demographic information to describe the sample of participants will be collected on the same occasion as the main interview. Interviews will last approximately one hour and will be conducted face-to-face, via telephone or video call, according to the Covid-19 sanitary situation and restriction measures.

With the consent of participants, interviews will be audio-recorded and transcribed in the languages in which they were conducted, using an accredited transcription company, to ensure data security. Interviews conducted in French will then be translated into English, since it is the language used for the analysis. All transcribed interviews will be checked by the research team to ensure accuracy and to remove information that could allow the identification of interviewees.

### Analyses

The quantitative analysis plan (see Appendix 1) includes: 1) descriptive statistics (description of categorical and quantitative variables, tests and estimation of confidence intervals); 2) bivariate analyses, subgroups comparisons and analysis of variations in time (baseline, three months, one year and four years), with appropriate tests to assess differences in groups (e.g. chi-square, Fisher and Student, Q Cochran); 3) multivariate regression models (cross-sectional and longitudinal) to model different patient reported outcomes such as comprehension of the information provided, general anxiety or cancer worry, and information-seeking behaviours. The data management and statistical analyses will be performed using Stata (StataCorp LP) and SPSS (IBM Corp). The main endpoint of this study will be measured at the end of the four years of intervention.

The qualitative data will support the interpretation of findings from the quantitative data. It will use framework analysis, a form of thematic analysis that facilitates the handling of large qualitative datasets [53]. It involves examining qualitative data to produce themes that summarise and interpret patterns of results. The analysis will take an explicit comparative approach, to investigate differences between England and France, and will also consider how the level of estimated risk affects reactions to risk-stratified screening and how acceptable the women found this. Coding will continue until the team is satisfied that codes and themes adequately describe and capture the data and that saturation has been achieved. Data will be stored and organised within Nvivo software (QSR International Pty Ltd. Version 12, 2018).

Dissemination of the study results will include the publication of research papers. A more direct feedback to investigators and to participants is planned at various stages of the trial.

## Discussion and conclusion

As of December 31^st^, 2021, 22,884 participants have been included and randomised in the trial and have completed baseline questionnaires. Inclusion for the qualitative study started in November 2021 in France and will start in March 2022 in the UK.

The Covid crisis resulted in a six-months suspension of trial enrolment as of March 2020, and still has a major detrimental impact on the recruitment, as successive epidemic waves continue to hinder both women and healthcare teams to participate in the study. Furthermore, when the enrolment reopened, one of the priorities was to reduce participants' time on site as much as possible. It was therefore decided to have women complete the first two questionnaires (STAI and Lerman cancer worry scale) at the inclusion site prior to randomisation, while the other questionnaires could be completed afterwards, either at the inclusion site or at home. This allowed the scientific requirements for assessing anxiety levels to be maintained prior to the start of the study, while adapting the conditions of inclusion to the health context.

One point to note is that the French Ethics committee limited the range of questionnaires proposed to women in France, due to concerns around heightened anxiety after answering the STAI-6 (Q1) and Lerman cancer worry scale (Q2). These questionnaires, however, will be administered in the five other countries taking part in the trial.

Along with investigating women’s perceptions of risk-based approaches and the socio-economic issues raised by this new form of screening, feedback is also needed on professionals’ perceptions of the MyPeBS trial and more generally on risk-based approaches. There is a dearth of research on clinicians’ views on implementing such approaches [54]. With this in mind, a complementary quantitative substudy is currently investigating professionals’ perceptions and attitudes regarding the risk-based breast cancer screening approach, the possible difficulties with giving information to women, delivering risk categories or announcing a change in the frequency of screening. The substudy will collect feedback on MyPeBS, on the training and communication tools provided to professionals by the study sponsor, on their overall satisfaction and on their specific difficulties encountered during recruitment and follow-up of participating women. If the risk-based strategy were to be implemented at a population level, having basic feedback from professionals on communication and training tools would be valuable. Moreover, getting information on their understanding of risk categories and genotyping will help specify their needs for further training.

Beyond the scientific and medical objectives of this clinical study, it is critical to pay attention to the consequences of such a paradigm shift for women on the one hand and for professionals on the other. Indeed, introducing a risk-based screening relying on individual biological differences also implies acknowledging non-biological differences (e.g. social status and health literacy) from an ethical perspective to ensure equal access to healthcare [21, 55]. Thus, through different methodologies and multidisciplinary work, this study aims to evaluate the potential psychological effects for women when their risk of developing breast cancer is assessed. It also aims to evaluate information needs, based on the evaluation of understanding of information transmitted at the time of entry into the study, and when they receive their risk category and their personalised screening schedule. These results will contribute to issuing of recommendations at the end of the trial to accompany any potential change in screening strategy at the European level, even though they should be adapted to specific local contexts. The description of the socio-economic categories of women who participated will also allow us to assess whether the study reached women of all socio-economic levels and whether interventions specifically dedicated to socio-economic categories with less participation should be put in place before generalisation.

## Data Availability

Not applicable.

## Appendix 1

### Statistical analysis plan

#### a. Software used

Data management and statistical analyses will be performed using Stata (StataCorp) and SPSS (IBM Corp).

#### b. Descriptive statistics

The categorical variables will be described by the numbers and percentages observed on each modality. Missing values will not be included in the calculation of percentages. The number of missing values will be indicated. In order to assess the uncertainty around the estimation, 95% confidence intervals according to exact binomial distribution will be estimated for the parameters of interest.

The quantitative variables will be described by the usual statistics: mean, standard deviation, median, minimum, maximum, first and third quartile. The other percentiles will be provided if necessary.

#### c. Bivariate analyses and subgroups comparisons

The bivariate analyses will mainly focus on detecting differences between subgroups (e.g., countries). Before, it will be ensured that each group contains a sufficient number of participants and is adequately powered.

For the qualitative or discrete variables, the significant differences between subgroups will be assessed either by means of the Chi-square test or by Fisher's exact test depending on the conditions of statistical validity (i.e., theoretical number strictly less than 5).

The Cochran Mantel Haentszel test (or Q Cochran) will test for equality of proportions in matched samples. It will be used to test, for instance, how the comprehension level of risk stratified screening varies in time, (i.e., between baseline, three months and four years).

For quantitative variables, significant differences between two subgroups will be detected via Analysis of Covariance (ANCOVA), controlling for baseline levels of those variables, and any other clinical or demographic variables that are not well balanced between subgroups, and hence may have a confounding effect. Initial assumption testing will include the Fischer test, which will be used to verify the hypothesis of equality of variances, and the Shapiro Wilk test, which will be used to verify the hypothesis of normality. In the case of non-normality, non-parametric approaches will be used in sensitivity analyses. In this case, the Wilcoxon or Mann–Whitney test for comparisons between two subgroups and the Kruskal–Wallis test beyond two subgroups will be considered.

The tests will be bilateral with a significance level of 5%. Adjustments for multiple comparisons (Bonferroni correction) do not appear to be required.

According to the literature, no method for managing missing data is unanimously accepted. As a result, automatic replacement of missing data will not be used [56]. The analyses will be conducted on all patients included with no missing data. In case of no answer, we will assume that the data are missing at random. This assumption will be tested by comparing the characteristics of respondents and non-respondents using the Chi-square statistic. Another source of missing data will likely come from women not answering subsequent waves of the survey (for instance, questionnaires at one year, two years or four years). In other words, we may face an attrition issue. First, we will test whether attrition is non exogenous (i.e., data are not missing at random), which could bias our estimates from longitudinal models assessing the evolution of our main dependent variables over time. In order to test for exogenous attrition, we will compare the results from the balanced (i.e., with no missing data) and unbalanced (i.e., with missing data points) panel using an Hausman test [57]. Rejection of the null assumption of equality of coefficients between the two panels will provide evidence of non-exogenous attrition. In case non exogenous attrition is detected, we will use inverse probability weighting to correct for the selection effect, i.e., we will weight women by the inverse of their probability of selection [58]. This method has been shown to reduce the selection bias in epidemiological applications.

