
In addition to the aforementioned issues which will be assessed globally and for each country, one further objective will be to compare the issues between countries. One of the strengths of the MyPeBS trial is the participation of six countries with specificities in terms of recruitment, local organisation of the trial and type of healthcare professionals involved. Adopting a comparative and contextualised perspective when analysing the results on acceptability of the trial, anxiety and cancer worry, understanding and information-seeking behaviours, equity, risk perception and intentions to change behaviour will offer a more nuanced view on the psychological and socio-economic issues at stake with risk-based approaches.

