### Procedure

Psychosocial questionnaires (see Fig. 1) are administered on the web platform to women at different times during the trial, namely at inclusion (baseline), at three months, at one year and at four years (end of trial). Women complete the baseline psycho-social and medical questionnaires before the randomisation process. Both steps are performed by the recruiter during the inclusion visit. For each other stage of the trial, women receive an invitation by email to complete the next questionnaires. Participants are given a one-month window and receive weekly email reminders to complete the three-months form online. At one year and four years, they are given a two-months window and bi-monthly reminders to fill in the forms. The study sponsor (Unicancer) is responsible for data management and ensures quality control, storage and exportation of data for dedicated analyses.

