#### Comprehension questionnaire (Q3) (at baseline, three months, and four years)

Patients' understanding of health information is a key issue in the exercise of their autonomy, and an ethical principle. This is why different texts—including legal, such as informed consent, or deontological, such as the code of medical ethics or the patient's charter—specify that the physician must provide the patient with a clear, fair and appropriate information on his or her health state, and on the investigations and care proposed. Providing information to the patient and ensuring that he or she understands is a necessary, even if not sufficient, condition for informed or shared decision-making to occur, and is a major public health issue, including in the case of breast cancer screening [36–38].

For all of these reasons, we decided to assess the comprehension of the information provided in MyPeBS. A comprehension questionnaire was developed based on our previous studies [27, 39] and on information tools used by investigators during the accrual visits. The questionnaire contains fifteen true/false questions divided into three categories: (i) general information on breast cancer; (ii) information on breast cancer risk; (iii) information on benefits and risks of breast cancer screening. As this questionnaire was developed for use in this specific study, the questionnaire was piloted amongst a set group of individuals: first, with three healthcare professionals to ensure the scientific relevance of the proposed questions, then with ten women aged 40 to 70. This pilot phase was carried out using face-to-face interviews based on an interview guide containing the main items (clarity of questions, length of questionnaire, redundant or missing questions, etc.) and also the "thinking aloud" procedure [40]. The content was analysed, and questionnaires were improved, on the basis of notes taken during these interviews and their recordings [41, 42].

The comprehension questionnaire will be administered to women at three months and four years. In order to test if responses are not due to pure chance, a Q Cochran test will be used to assess this.

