##### d.2. Longitudinal models

In order to analyse the changes of an outcome variable with time, longitudinal (or panel) data models will be estimated. The estimated models belong to the family of generalised linear mixed models (GLMMs). The link function and distribution of error terms will be defined depending on the nature of the dependent variable. In the GLMMs models, only the intercept will be specified as random in order to capture repetition of data across individuals. It will also be possible to account for various levels of heterogeneity across countries by including country specific random effects (multilevel model). Time-fixed effects will be included in the model to assess changes of a dependent variable over time, and interactions between time-fixed effects and regressors of interest will be included to test for changes in the impact of a variable over time. Potential attrition bias will be assessed and accounted for using the methods described above (missing data management).

## Appendix 2

Table

**Table 1 Tab1:** Summary of objectives, statistical analyses and tools

Objective	Tools	Timing	Analysis
Assess the psychological impact of risk communication on women	- STAI (Q1) - Lerman’s cancer worry (Q2) - Qualitative interviews	Baseline, 3 months, 1 year, 4 years	- Comparisons between two experimental arms, controlling for baseline levels and other covariates where required
Assess women’s comprehension of the information provided within MyPeBS, and their willingness to search for further information	- Comprehension questionnaire (Q3) - Information seeking behaviours questionnaire (Q4) - Qualitative interviews	Baseline, 3 months, 4 years	- Comparisons between arms and correlations between women’s information comprehension level, information-seeking behaviours and socio economic and demographic characteristics - Correlations with psychological characteristics (anxiety, cancer worry)
Analyse MyPeBS participants' socio-economic and demographic characteristics as well as quality of life	- Quality of life (Q6) - Socio-demographic questionnaire (Q8)	Baseline, 4 years	- Comparisons between arms of women’s socio-economic characteristics and quality of life, focus on health inequalities. Use equality of proportion or Student test to compare the distribution of the variables across the two harms - Correlations with risk perceptions and screening uptake

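### Comparisons of outcome levels between countries ignore clustering by inclusion site or recruiter, so their false-positive rate exceeds 5% if outcomes vary between sites within a country

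*Protocol article*

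**What the plan says.** The Objectives section states that "one further objective will be to compare the issues between countries". Sample size justification refers to this as the sixth objective and says it will be well powered.

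Appendix 1, section c, gives the main purpose of the bivariate analyses: "The bivariate analyses will mainly focus on detecting differences between subgroups (e.g., countries". For qualitative or discrete variables, "the significant differences between subgroups will be assessed either by means of the Chi-square test or by Fisher's exact test". For quantitative variables, "significant differences between two subgroups will be detected via Analysis of Covariance (ANCOVA), controlling for baseline levels of those variables". Mann-Whitney (two groups) and Kruskal-Wallis (more than two) serve as sensitivity analyses under non-normality. Tests are two-sided at 5%. The one safeguard stated for subgroup comparisons is a check that each group is large enough and adequately powered.

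Section d.1 (cross-sectional models) offers heteroscedasticity-consistent standard errors. Section d.2 (longitudinal models) says "In the GLMMs models, only the intercept will be specified as random in order to capture repetition of data across individuals" and allows country random effects as an option. No section mentions inclusion site or recruiter.

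On how women enter the study, Participants says the recruiter obtains consent. Procedure says of the baseline questionnaires and randomisation that "Both steps are performed by the recruiter during the inclusion visit". The comprehension questionnaire was built in part on "information tools used by investigators during the accrual visits". Discussion and conclusion refers to questionnaires completed at the inclusion site.

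**The concern.** Women are randomised individually, but they are not allocated to countries. A country mean is an average over the sites that took part in that country. Women handled by the same recruiter, or informed at the same site, may share part of their outcome. This is most plausible for comprehension of the information given and for satisfaction with information and organisation.

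A test that counts each woman as an independent observation then credits the country mean with more information than it holds. Ordinary site-to-site variation can appear as a country difference. The group-size check in section c does not help: for a fixed number of sites, more women per site makes the problem worse. Nor does a country random effect, because the omitted correlation lies between women within a country. Heteroscedasticity-consistent errors allow for unequal variance but not for correlation.

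At stake is the reliability of reported country differences, which the Objectives section intends for a contextualised reading of the results.

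**Working it through.** **1. The plan's own figure.** Sample size justification assumes 70% follow-up of the first 22,000 women: 0.70 × 22,000 = 15,400, or 7,700 per arm. For a standardised difference of 0.08, the expected z is 0.08 × √(7,700/2) = 4.96. Two-sided power is Φ(4.96 − 1.96) = Φ(3.00) = 99.9%. The stated power of over 99% is reproduced. It concerns the two arms; no figure is given for countries.

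**2. Inputs for the country comparison.** From the article: 15,400 women, six countries, two-sided 5%. Assumed, because the article gives neither: the number of sites and the site ICC. Also assumed: equal countries, equal sites and no true country difference.

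**3. Formulas.** With m women per site, the design effect is DE = 1 + (m − 1) × ICC. The actual error of a nominal 5% test that ignores sites is:

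- two countries: 2 × [1 − Φ(1.96/√DE)]
- six countries: P(χ² on 5 df > 11.07/DE)

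**4. Worked case.** With 150 sites, m = 15,400/150 = 102.7. At ICC 0.01, DE = 1 + 101.7 × 0.01 = 2.02.

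- Two countries: 1.96/√2.02 = 1.38, giving 17%.
- Six countries: 11.07/2.02 = 5.49, giving 36%.

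**5. Range at 15,400 women** (two countries / six countries):

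| Sites (women per site) | ICC 0.001 | ICC 0.005 | ICC 0.01 | ICC 0.05 |
|---|---|---|---|---|
| 60 (257) | 8% / 12% | 19% / 43% | 30% / 68% | 60% / 98% |
| 150 (103) | 6.2% / 7.4% | 11% / 20% | 17% / 36% | 43% / 87% |
| 300 (51) | 5.6% / 6.1% | 8% / 12% | 11% / 20% | 30% / 68% |
| 1,000 (15) | 5.2% / 5.3% | 5.8% / 6.6% | 6.7% / 8.5% | 14% / 27% |

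At full recruitment with the same follow-up, 0.70 × 85,000 = 59,500 women. At ICC 0.01 the rates are then 26% / 59% with 300 sites and 12% / 22% with 1,000 sites.

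**6. When the error doubles to 10%.** This needs DE = 1.42 for two countries and 1.20 for six. At ICC 0.01, DE = 1.20 corresponds to m = 1 + 0.20/0.01 = 21 women per site.

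**7. Simulation check.** With 4,000 runs per setting, 25 equal sites per country and ICC 0.01, ignoring sites gave 16% / 36%, in line with step 4. Unequal site sizes (coefficient of variation 0.8) raised this to 22% / 52%. A site-level analysis stayed between 4.3% and 5.5% in every setting.

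**8. The arm comparison.** A simulated arm-by-country test that ignored sites (3,000 runs, about 2,566 women per country, site intercepts only) rejected in 4.5% and 3.9% of runs with 20 sites per country (ICC 0.01, 0.05), and in 5.0% and 4.1% with 100 sites. The corresponding rates for country means were 42%, 91%, 13% and 41%. Shared site intercepts cancel between arms, so the inflation is confined to country means.

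**The case against.** The strongest reply is that the size is unknown. The article gives no number of sites and no ICC, and with many small sites or a very small ICC the error stays near 5% to 8%. That stands. A reader might infer that country differences will be falsely declared far more often than 5% of the time; the documents support this only conditionally.

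The planned ANCOVA adjusts for baseline, which the calculation does not, and this may shrink the residual ICC for outcomes with a baseline. That stands too. It does not help the information-seeking (Q4) and satisfaction (Q7) questionnaires, which have no baseline, or the plain chi-square and Fisher tests.

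The clustering evidence should not be stretched:

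- Women are not recruited in groups; they are invited or volunteer individually.
- The private offices, screening centres and hospitals in Participants are places where study information was disseminated, not a list of enrolment settings.
- The Objectives section mentions "specificities in terms of recruitment, local organisation of the trial and type of healthcare professionals involved" as features of the six countries, so it is not direct evidence of variation within a country.
- Later questionnaires are completed online after an email invitation.

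The recruiter's role at the inclusion visit remains as the route to clustering.

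The stakes can be overstated as well. The Background's remark on generalisability concerns the comparison of the two screening approaches, which randomisation protects. The Discussion foresees European recommendations adapted to local contexts, not country-specific recommendations drawn from significance tests.

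Finally, the random-intercept sentence in d.2 most naturally excludes random slopes rather than a site level, and a condensed article may leave detail to a fuller plan. But Appendix 1 does name the tests for country differences, and its multilevel option stops at country. The criticism is of that stated choice.

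**Conclusion.** The point holds for comparisons of outcome levels between countries. The named tests treat women as independent, nothing in sections c, d.1 or d.2 accounts for site or recruiter, and any positive within-country site correlation takes the error above 5%.

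The size is conditional on the assumed sites and ICC. At 15,400 women, 150 equal sites and ICC 0.01 give about 17% (two countries) and 36% (six). ICC 0.001 with 150 or more sites gives about 5% to 7%, and 1,000 sites at ICC 0.01 give 6.7% / 8.5%. Fewer or unequal sites, or a larger ICC, give more.

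Two limits apply. A reader might infer that the arm comparison is compromised; it is not, since women are randomised individually and shared site intercepts cancel. Site-varying arm effects were not examined. For the anxiety and cancer-worry scales (Q1, Q2), France does not administer the questionnaires, so the comparison covers five countries and the six-country figures do not apply.

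**What to change.** In Appendix 1, sections c and d.2, state that comparisons of outcome levels between countries use country as a fixed factor with a random intercept for inclusion site (or recruiter) nested in country, or standard errors clustered on inclusion site. For binary and ordinal outcomes, use the corresponding mixed or cluster-robust logit. In the longitudinal models, add the site level above the woman. Report plain chi-square, Fisher and Kruskal-Wallis results for countries as descriptive only. State that Q1 and Q2 are compared over five countries.

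The cost is analysis-plan wording and one more model level or a clustered-variance option in Stata, which is already named as software. No new data are collected, but the change relies on a site identifier that the registration platform is assumed to hold. Confidence intervals for country differences will be wider, so the claim that the sixth objective is well powered should be rechecked with a stated number of sites and ICC.
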